### Design

This evaluation study is a prospective non-randomized, matched control, before-and-after study [28]. We will compare all hospitalised patients meeting the inclusion criteria with patients receiving usual care in a control setting. The PACT model is directed at the organisational level or geographic site, affecting all patients within the uptake area. Therefore, the intervention and controls are separated in different hospitals to avoid contamination. The chosen design improves comparability between the patient populations by matching them on factors known to be important for outcomes (age, sex and number of conditions), adjusting for baseline differences between the populations with a before-after design and adjusting for known confounders by the propensity score method [29, 30].

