### Participants

The intervention group participants will be recruited consecutively until we have reached the target of 600 patients. As soon as the patients have signed the consent form, the intervention will start and the baseline data collection will begin. The follow-up period will be one year from the initial assessment for each patient.Inclusion criteria: Patients with emergency admission to the UNN internal medicine department in Tromsø and Harstad who are over the age of 65 years, have two or more long-term conditions and provide valid written informed consent (either by the patient or the next of kin).Exclusion criteria: Language barriers, life expectancy of less than three months and unable to provide written informed consent.

The control population will be recruited from the Nordland Hospital in Bodø and from the hospital UNN Narvik. When an index patient is identified in the hospitals using patient-centred teams, at least two eligible patients from the control hospitals will be identified. Sex, age and number of long-term conditions will be used to match the control patients to the index patients. The control patients will be subject to the same data collection as the intervention patients.

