### Sample size

The sample size calculation is based on the primary outcome measure: the Short Form Health Survey (SF-36). The SF-36 has a range from 0 to 100, where 100 is the best possible score, and a standard deviation (SD) of approximately 25 in other populations. Points of two have been shown to be clinically significant [31]. Two different geriatric integrated care interventions similar to ours found differences of 4–6 points between intervention and control groups [32, 33]. We wish to be able to detect a difference of four points in the SF-36 physical health dimension between the intervention and control groups. With 600 patients in each group and a statistical significance level of 0.05, we will have a power of 0.80 to detect such a difference between the groups. We expect this to be realistic based on the existing hospital admission rates. The intervention and control hospitals had approximately 9500 medical emergency admissions for patients aged 67 years and older in 2014 [2].

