#### Analyses

The analyses will use an intention-to-treat approach that includes all participants who signed the informed consent at the intervention and control hospitals. Missing data will be imputed using multiple imputations [48]. The multiple imputation model will include predictors from all time points, including health-related quality of life (SF-36), background variables, trial-related variables and resource use at baseline. Results with and without imputed data will be reported. The data will be analysed as a synthetic randomised controlled trial (RCT), using the propensity score method. This method postulates that each patient has a basic probability of the outcome of interest based on his/her characteristics [29]. Based on available knowledge for each patient (e.g. age, sex, education, ethnicity), we can calculate the patient’s propensity for the outcome (i.e. change in QoL). In subsequent analyses, we stratify analyses by this score. Within each stratum, the only known difference between patients with respect to the outcome will be the patient-centred teams. The fundamental requirement for validity in a causal analysis is that the variables used to create the propensity score are independent of the probability of getting the intervention. In common-sense terms, this means that in the synthetic study, within the same propensity score strata, the assignment to treatment is essentially the same as if it had been done by randomisation.

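### The stated primary analysis only stratifies on a score and has no explicit term for the matching factors, so some precision goes unused and balance on number of long-term conditions is not assured

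*Protocol article*

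**What the plan says.** The Participants section describes individual matching: "Sex, age and number of long-term conditions will be used to match the control patients to the index patients". For each index patient, "at least two eligible patients from the control hospitals will be identified"; the ratio finally enrolled is not given. The Design section explains that comparability comes from "matching them on factors known to be important for outcomes (age, sex and number of conditions"), together with before-and-after adjustment and a propensity score for known confounders.

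The Sample size section aims to "detect a difference of four points in the SF-36 physical health dimension between the intervention and control groups", takes "a standard deviation (SD) of approximately 25 in other populations", and concludes: "With 600 patients in each group and a statistical significance level of 0.05, we will have a power of 0.80". It mentions no within-set correlation and no paired method.

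The Analyses section builds the score as follows: "Based on available knowledge for each patient (e.g. age, sex, education, ethnicity"). It continues: "In subsequent analyses, we stratify analyses by this score". As worded there, the score predicts the outcome (change in quality of life), although the method is called a propensity score. The section does not mention matched sets or covariates in an outcome model. Number of long-term conditions is the only one of the three matching factors not given as an example.

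**The concern.** Matching on prognostic factors makes the two groups alike on those factors. That has two consequences for the analysis.

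- **Precision.** Part of the outcome variance is shared within matched sets. A standard error that ignores this is too wide unless the analysis uses the set or adjusts the outcome for the matching factors. Stratifying on a treatment propensity score does neither well. After matching, these factors hardly predict which group a patient is in, so they carry little weight in such a score.
- **Balance.** Matching balances number of conditions over the whole sample. It does not balance it within strata formed on other variables. If those variables differ between sites and are related to number of conditions, stratifying on a score that omits it can create a difference within strata that was absent overall. The Analyses section claims that, within a stratum, the team intervention is the only known difference bearing on the outcome. For a factor the Design section treats as prognostic, that claim would then not be assured.

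**Working it through.** **Inputs from the article:** difference 4 points, SD 25, 600 per group, significance level 0.05 (two-sided reproduces), power 0.80. **Not in the article:** the within-set correlation r, the share of variance explained by the matching factors, and site differences in education. All values used for these are assumptions.

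**1. The plan's own figure.** For an unpaired comparison:

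- SE = 25 × √(2/600) = 1.44
- z = 4/1.44 = 2.77
- power = Φ(2.77 − 1.96) = 0.791
- n for 80% power = 2 × (1.96 + 0.842)² × 25²/4² = 614 per group

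This agrees with the stated 600 and 0.80 to rounding. A one-sided test does not fit (power 0.870 at 600). The calculation is therefore unpaired and takes no credit for matching.

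**2. What ignoring the matching costs.** Illustrated with 600 pairs at 1:1:

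- Test ignoring the sets: power = Φ((2.77 − 1.96)/√(1 − r)); true type I error = 2 × (1 − Φ(1.96/√(1 − r)))
- Matched test: power = Φ(2.77/√(1 − r) − 1.96)

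| r (assumed) | Power, sets ignored | True type I error | Power, matched | Gain (points) |
|---|---|---|---|---|
| 0.05 | 0.797 | 0.044 | 0.811 | 1.4 |
| 0.10 | 0.804 | 0.039 | 0.832 | 2.8 |
| 0.20 | 0.818 | 0.028 | 0.873 | 5.5 |

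**3. Whether the stated stratification recovers this.** Under exact matching, r equals the share of variance that the matching factors explain. Taking that share as 10%:

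- paired analysis: SE 1.37
- outcome model with the three factors as covariates: 25 × √(0.9 × 2/600) = 1.37
- five strata on an outcome score containing the factors: about 1.38 to 1.40 (simulation)
- five strata on a treatment propensity score: about 1.44 (simulation), the same as the unmatched value in step 1

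The answer therefore depends on which score is meant. Adding number of conditions to a treatment score protects balance, but it does not narrow the standard error. Covariates in the outcome model do.

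**4. Balance on number of conditions if it is not in the score.** Two sets of assumed inputs, both with exact matching:

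- *Milder.* Education is binary, differs between groups by a log-odds of 0.5 to 1.0, and falls by 0.2 to 0.4 log-odds per condition. The within-stratum difference is 0.05 to 0.17 conditions. At an assumed 3 points per condition, that is 0.05 × 3 = 0.15 to 0.17 × 3 = 0.51 points.
- *Stronger.* Education differs by 0.5 SD and correlates −0.4 with number of conditions. Strata on a treatment score of age, sex and education give a within-stratum difference of about 0.18 SD in conditions. With a true effect of zero, the estimates were −0.9, −1.1 and −1.8 points when the matching factors explained 5%, 10% and 20% of the variance.

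With number of conditions added to the score, the within-stratum difference was 0.00 and the bias was about zero.

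**The case against.** The strongest reply is that nothing the protocol promises is broken. The primary outcome is an adjusted difference in change. Breaking matched sets is valid when the matching factors are adjusted for, and two of the three are named for the score. Full covariate lists and variance methods normally belong in an analysis plan, which is not shown here. Much of this stands, and it rules out several stronger readings that a reader might draw.

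- *The sample size is wrong.* Not supported. Ignoring a positive within-set correlation is conservative. On the figures above, even the test that ignores the sets has power of about 0.80 or more, with type I error below 0.05.
- *The precision gained by matching is thrown away.* Too strong. If the score predicts the outcome, as the Analyses section literally says, most of the precision is recovered. It goes unused only if the score predicts treatment, which is what the term propensity score and the comparison with randomisation suggest.
- *Number of conditions is excluded from the score.* Not established. The list is one of examples, and the Design section says known confounders are handled by the score.
- *The gain is large.* A correlation of 0.5 would give a matched power of 0.975, but nothing in the article supports that value. The outcome is a change score and there are only three matching factors, so a low value is more plausible.
- *A matched-set term is required.* It is not. The enrolled ratio is not stated, so a 1:1 paired formula is only illustrative, and covariate adjustment achieves nearly the same.

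The reply does not remove the point that the article fixes stratification on a score as the analysis and leaves open which kind of score it is. Under one of the two readings the matching factors do not improve precision.

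**Conclusion.** The point holds as a modest, low-cost improvement. The design matches on three prognostic factors, and the stated analysis does not explicitly carry them into the estimate. Under a treatment propensity score, the likely cost is roughly 1 to 6 points of power (r of 0.05 to 0.2), in the conservative direction. If number of conditions is also left out of the score, a bias of about 0.1 to 1 point is possible. It reaches 1.8 points only under the strongest assumptions tried: the larger education gap, with the matching factors explaining 20% of the variance.

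The precision figures rest on an assumed correlation, exact 1:1 matching, and the article's SD of 25 applied to the change score. The size and sign of the bias depend on assumed site differences in education and an assumed link between education and number of conditions. They show that the mechanism can matter, not that it will occur. The sample size needs no change.

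**What to change.** In the Analyses section:

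1. Name age, sex and number of long-term conditions as covariates in the primary outcome model, alongside the score strata. This is the step that recovers the precision.
2. Name the same three variables as members of the score, and say whether the score predicts treatment or outcome.
3. Report balance on the three factors within strata.
4. Optionally, keep a matched-set identifier and use a set-level random effect or set-robust standard errors. Either works with any enrolled ratio, and a random effect keeps patients whose match is lost. It adds little beyond step 1.

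The cost is a few sentences of analysis wording and, for step 4, one identifier in the dataset. The three variables are already needed for matching, and no additional patients or data collection are required.

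### The Analyses section misdefines the propensity score and its validity condition: a score that met the stated condition could not adjust for confounders

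*Protocol article*

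**What the plan says.** The study is not randomised, and intervention and control patients come from different hospitals. The Design section lists three means of achieving comparability: matching on age, sex and number of conditions, a before-after comparison, and "adjusting for known confounders by the propensity score method".

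The Analyses section, under Effectiveness evaluation, describes the third of these:

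- Basis of the score: "This method postulates that each patient has a basic probability of the outcome of interest based on his/her characteristics".
- Inputs, given as examples: "Based on available knowledge for each patient (e.g. age, sex, education, ethnicity").
- Quantity computed: "we can calculate the patient’s propensity for the outcome (i.e. change in QoL").
- Use: "In subsequent analyses, we stratify analyses by this score".
- Validity condition, which the section calls fundamental: "the variables used to create the propensity score are independent of the probability of getting the intervention".
- Property claimed within strata: "the assignment to treatment is essentially the same as if it had been done by randomisation".

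No other section of the article defines the score differently or corrects these statements.

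**The concern.** The section describes a prognostic score and calls it a propensity score. It then attaches a condition that fits neither. A propensity score is the probability of being in the intervention group given baseline covariates. Stratifying on it removes confounding if, given those covariates, group is independent of the potential outcomes and the groups overlap. Confounders are by definition related to group, so they are exactly the variables that the stated condition does not allow.

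The primary outcome is an adjusted between-group difference in SF-36 change, and stratification on this score is the covariate adjustment that the Analyses section describes for it. The Discussion names lack of randomisation as the main limitation. An analyst who took the paragraph at its word could build the wrong score, or doubt whether a variable such as education may enter if it differs between hospitals. A later analysis plan that defined the score correctly would contradict the published one.

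**Working it through.** **1. The plan's own figure.** The Sample size section gives 600 per group, a difference of 4 points, SD about 25, significance level 0.05 and power 0.80. Taken as two-sided:

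- Standard error = 25 × √(2/600) = 1.443, and 4/1.443 = 2.771.
- Power = Φ(2.771 − 1.960) = Φ(0.811) = 0.791.
- n for power 0.80 = 2 × 25² × (1.960 + 0.842)² / 4² = 614 per group.

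The stated figure reproduces within rounding and is not affected by this point. It supplies the 4-point yardstick used below.

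**2. The statements side by side.** Design wants the score to deal with confounders. Analyses requires its variables to be unrelated to group. A confounder must be related to both group and outcome, so no variable can be a confounder and also meet the condition. The two sections cannot both hold.

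**3. Algebra for a simple case (assumed values).** Let c be a confounder with SD 1 and mean higher by δ in one group. Let x be a prognostic variable with SD 1, independent of c and unrelated to group. Each is worth 10 points of outcome per SD.

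- *Score built only from group-independent variables (x).* Within a stratum of x, the groups still differ by δ on c. The bias is 10 × δ: 2, 3 and 5 points for δ = 0.2, 0.3 and 0.5, the same as the crude bias.
- *Outcome score that includes the confounder, s = c + x.* At fixed s, the mean of c is s/2 + δ/2 in the shifted group and s/2 in the other. The mean of x is s/2 − δ/2 and s/2. The expected outcome, 10 × s, is equal, so the bias cancels. Yet at δ = 0.2 the groups differ by +0.1 on c and −0.1 on x within the stratum. Assignment is therefore not as if randomised, even though the effect estimate is protected.

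**4. Simulation of the same case.** 1,000 runs, 600 per group, true effect 0, outcome SD √(100 + 100 + 425) = 25, five strata. Mean estimate, which here is the bias, in points:

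| Imbalance δ (SD) | Crude | Outcome score, group-independent variables only | Outcome score including the confounder | Treatment propensity score including the confounder |
|---|---|---|---|---|
| 0.2 | 2.00 | 2.01 | 0.21 | 0.21 |
| 0.3 | 2.99 | 2.99 | 0.28 | 0.28 |
| 0.5 | 4.97 | 4.97 | 0.50 | 0.49 |

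The literal condition removes nothing. A treatment propensity score that includes the confounder removes about 90%, for example (2.00 − 0.21)/2.00 = 0.895. The outcome score that includes the confounder does as well. The damage therefore comes from the independence condition, not from the outcome basis alone.

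**The case against.** The strongest reply is that the paragraph is a garbled account of a sound intention. Education is named as an input, Design states the purpose as confounder adjustment, and the sentence after the condition speaks of assignment within strata. On that reading the authors meant that covariates are unrelated to group within score strata. This is plausible as to intent. It does not rescue the text, because that balancing property belongs to a score for group membership, and the section defines a score for change in quality of life.

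Four stronger readings are tempting, and the document does not support them:

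- *Confounders would be dropped.* The article gives no variable-selection rule. The sentence is a validity condition, and at least one variable that may differ between hospitals is listed as an input.
- *The primary comparison would have no protection.* Only the score step is affected. Matching and the before-after comparison remain.
- *The trial faces 2 to 3 points of bias.* Those figures follow by construction from assumed inputs once the only confounder is kept out of the score. The simulation has no baseline measurement, and a confounder that shifts baseline and follow-up equally causes no bias in change. The 10 points must therefore be read as an effect on change. The SD of 25 is quoted for SF-36 scores and is only assumed for change.
- *An outcome score is harmful in itself because it would use follow-up data that the intervention has altered.* The section does not say in which group the score would be fitted. Fitted on both groups or on controls alone, a score including the confounder left about the same small bias when the true effect was zero.

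**Conclusion.** The point stands as an error in the text. The score is misdefined, its validity condition is wrong and conflicts with the Design section, and the within-stratum claim does not follow from an outcome score. This is a misstatement of the adjustment step in a non-randomised primary comparison, not detail left to an analysis plan.

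If the condition were followed literally, the score step would remove none of the confounding. That conclusion does not depend on the simulation inputs. Its size in points does: 2 to 3 points for an imbalance of 0.2 to 0.3 SD in a confounder worth 10 points of change per SD, against a 4-point target. This is an illustrative worst case, not an estimate for this trial. If the analysts in fact include the confounders, as the named inputs suggest, the bias would be largely removed and the fault would lie in the description.

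**What to change.** In the Analyses section:

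1. Define the score as the probability of being an intervention-hospital patient given baseline covariates that the study already collects, including baseline SF-36, age, sex, number of long-term conditions and education. State that it is estimated without outcome data.
2. Replace the independence sentence with the correct condition: given these covariates, group is independent of the potential outcomes, and the groups overlap.
3. State that covariate balance is checked within score strata, and make the as-if-randomised statement conditional on step 2.

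The model form and the full covariate list can stay in the analysis plan. Frailty and a fixed look-back for earlier admissions should not be assumed available, since the article does not show that either is recorded.

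The cost is a change of wording. It needs no new patients, procedures or data and leaves the sample size unchanged.

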### Cost-effectiveness evaluation

#### Trial-based economic evaluation

The trial-based economic evaluation consists of a cost-utility analysis with a time horizon of 12 months. The analysis takes a health provider perspective and collects data on health resource use and health outcomes measured in quality-adjusted life-years (QALYs). The economic evaluation will be conducted in accordance with the CHEERS statement [49].

For the economic evaluation, health outcomes will be measured using the SF-6D instrument [50]. The SF-6D will be extracted from the SF-36 and will include physical functioning, role participation (combined role-physical and role-emotional), social functioning, bodily pain, mental health and vitality. The algorithm by Brazier et al. will be used to transform the scores into utility values [51]. The SF-6D scores will be transformed to QALYs by weighing the per-period estimates of utility scores with the time spent in the particular health state, assuming a linear change in utility over time. Imbalances in baseline values will be adjusted for using multiple regression [52].

Only health care costs assumed to be affected by the PACT model and of potential economic significance will be included in the main analysis. Costs borne by patients and productivity losses to society are considered less relevant for the patient group in this study. Two main cost components will be included: the costs related to the PACT model (technology and personnel costs) and the cost related to health services use over the course of the trial (hospital inpatient, outpatient, day hospital and emergency services, community-based health care services and medication). Cost weights will be applied to calculate the costs associated with each primary and secondary health resource activity. These will be collected from hospital accounting databases, national tariffs and official wage and price lists.

The cost-utility analysis will be based on the net-monetary benefit framework (NMB). The NMB approach allows for modelling the variability in the cost effectiveness between the centres and GPs [53]. NMB regression will be used to analyse whether the PACT model is more cost effective for a specific subgroup of patients (the effect modification in RQ 5).

The data will be analysed using appropriate techniques that account for the correlation between cost and effect data. Trial-wide costs, QALYs and incremental cost-effectiveness ratios will be reported, as will hospital-specific estimates. If the economic evaluation finds that one option ‘dominates’ the other with a negative incremental costs (costs less) and a positive incremental effect (produces more QALYs), this will considered the most cost-effective option. If better outcomes are associated with higher costs, an incremental cost effectiveness ratio (ICER) will be calculated [54]. Cost effectiveness will then be assessed based on different willingness-to-pay (WTP) thresholds.

Sampling uncertainty will be handled through the use of p-values and confidence intervals (CIs) for costs, QALYs and incremental cost-effectiveness ratios. Confidence intervals for the mean differences in costs and effects between groups will be calculated using non-parametric bootstrap simulation. Cost-effect pairs will be plotted in the cost-effectiveness plane and show the 95 % confidence regions for the ratio. A range of different thresholds will be analysed using a cost-effectiveness acceptability curve.

Non-sampling uncertainty will be handled in sensitivity analyses. The most uncertain methodological assumptions will be varied to illustrate the robustness of the results. Sensitivity analyses will be performed on perspective (societal versus health provider) and different willingness-to-pay values.

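### Because each hospital delivers only one arm, centre variability in cost effectiveness is not estimable, and the promised p-values and intervals for the ICER should give way to net-benefit inference

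*Protocol article*

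**What the plan says.** All three statements are in the protocol article, under Trial-based economic evaluation.

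- Site results: "Trial-wide costs, QALYs and incremental cost-effectiveness ratios will be reported, as will hospital-specific estimates". The net-monetary-benefit (NMB) framework is said to allow "modelling the variability in the cost effectiveness between the centres and GPs".
- Uncertainty: sampling uncertainty is to be handled by "p-values and confidence intervals (CIs) for costs, QALYs and incremental cost-effectiveness ratios". The same section plans bootstrap intervals for the mean differences in cost and effect, a cost-effectiveness plane with 95% regions for the ratio, and an acceptability curve. An ICER is calculated when better outcomes come with higher costs.
- Perspective: a sensitivity analysis will set a societal perspective against the provider perspective, although "Costs borne by patients and productivity losses to society are considered less relevant for the patient group in this study".

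The Design section says that "the intervention and controls are separated in different hospitals to avoid contamination". Under Participants, the intervention group is "Patients with emergency admission to the UNN internal medicine department in Tromsø and Harstad", and controls come from Nordland Hospital in Bodø and UNN Narvik.

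**The concern.** Cost effectiveness is an increment: PACT minus usual care. Its variability between centres is a centre-by-treatment effect, which can be learned only where centres contain both arms. Here none does. The before measurement does not help, because it is each patient's own baseline at consent and not a usual-care cohort followed for 12 months at the same hospital.

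For the ICER, a p-value needs a null hypothesis, and none is stated. The interval behaves badly when the denominator, the QALY difference, is near zero.

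The Discussion says that local authorities may use the results to decide whether to keep funding PACT and whether to extend it to other hospitals. A site-level ICER read as the effect of PACT at that hospital, or an ICER interval with no sensible reading, would bear directly on those decisions.

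**Working it through.** **The plan's own figure.** The economic sections state no numbers. The sample size does: 600 per group, a 4-point difference, SD 25, alpha 0.05, power 0.80. The SE is 25 × √(2/600) = 1.443, and power = Φ(4/1.443 − 1.96) = Φ(0.811) = 0.79 (two-sided). The figure reproduces, and 600 per arm is used below.

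**Part 1: what the hospitals can identify.** Write μ(h, a) for the mean net benefit at hospital h under arm a. Four hospitals and two arms give eight means. Four are observed: PACT at Tromsø (T) and Harstad (H), usual care at Bodø (B) and Narvik (N). No hospital has both of its means observed.

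| Hospital | PACT | T | H | B | N |
|---|---|---|---|---|---|
| Tromsø | 1 | 1 | 0 | 0 | 0 |
| Harstad | 1 | 0 | 1 | 0 | 0 |
| Bodø | 0 | 0 | 0 | 1 | 0 |
| Narvik | 0 | 0 | 0 | 0 | 1 |

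The PACT column is the sum of columns T and H, so the rank is 4 for 5 parameters. More patients do not change this.

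A contrast for one PACT hospital can still be calculated. For Tromsø against its matched controls C it equals

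[μ(T, PACT) − μ(T, usual)] + [μ(T, usual) − μ(C, usual)].

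The first bracket is the effect wanted. The second is the difference between hospitals under usual care, and no data from the study separate the two. Matching on sex, age and number of conditions removes only patient mix on those factors. For Bodø and Narvik no increment of their own exists, only mean costs and QALYs.

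To give a scale, assume a hospital ICC of 0.01 to 0.05 on the SF-36. Two hospitals then differ by chance with an SD of 25 × √(2 × ICC), which is 3.5 to 7.9 points, against a target effect of 4. The ICC is an assumption, and the corresponding figure for net benefit is unknown.

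**Part 2: the ICER.** The null ICER = 0 only says that the cost difference is zero, which has its own test. The null ICER = λ (λ being willingness to pay) says that λ × ΔQALY − Δcost = 0, which is the test of incremental net benefit at λ. So a p-value for the ratio adds nothing.

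For the interval, the Fieller 95% set is bounded only if |ΔQALY| > 1.96 × SE. With SE = SD × √(2/600) and an assumed SD:

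| QALY SD (assumed) | SE | 1.96 × SE | Share of replicates with opposite QALY sign at a true difference of 0.01, Φ(−0.01/SE) |
|---|---|---|---|
| 0.12 | 0.0069 | 0.014 | 7% |
| 0.20 | 0.0115 | 0.023 | 19% |

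A numerical illustration assumes a cost difference of 20,000 currency units, cost SD 200,000, no correlation and QALY SD 0.15:

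| QALY difference | 95% set for the ICER |
|---|---|
| 0.005 | the whole line |
| 0.010 | everything except −1,793,762 to −332,541 |
| 0.015 | everything except −9,314,849 to −190,854 |
| 0.020 | −137,618 to 7,288,136 |
| 0.030 | −89,433 to 2,050,602 |

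Incremental net benefit, λ × ΔQALY − Δcost, has variance λ² × var(ΔQALY) + var(Δcost) − 2λ × cov. Its interval is finite at every λ, whatever the QALY difference.

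**Minor part: societal perspective.** The sources named under Outcome measures, Data collection and management, and Trial-based economic evaluation are health service use, PACT costs, and self-reported lifestyle, socio-economic status and care experiences. Patient expenses, informal care and productivity are not named.

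**The case against.** On sites, the promise of hospital-specific estimates can be met by mean costs and QALYs per hospital, and each PACT hospital can be compared with its matched controls. Site results also have a purpose, because the article says that local implementation will vary. Confounding of arm with hospital affects the trial-wide result too, and the Discussion concedes both the lack of randomisation and the small number of hospitals. The sentence on NMB describes what the method can do; the regression actually promised there is for patient subgroups. Most of this stands, so a reader who infers that site results carry no information goes too far. What remains is that the article does not say which estimate is meant or that it is a between-hospital contrast, and that the capability credited to NMB cannot be exercised for centres in this design.

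On the ICER, Fieller or bootstrap intervals are valid when the QALY difference is clear of zero: at 0.03, under 0.5% of replicates change sign under the SDs above. The plan already has NMB, the plane and the acceptability curve, and its bootstrap is specified for mean differences, so it does not say that ratios from different quadrants will be pooled. This stands. But the condition for calculating an ICER concerns the direction of the results, not how clearly the QALY difference departs from zero, so it does not prevent an unbounded interval. The p-value is still promised.

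Two further readings are tempting. One is that the societal analysis must merely repeat the provider result. The article does not support that: costs called less relevant for the main analysis may still be collected or assumed, and the full protocol is not shown. The other is that lower cost with fewer QALYs is left out. The dominance rule is worded symmetrically, and NMB and the acceptability curve cover all four quadrants.

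**Conclusion.** The point holds for two statements. Centre variability in cost effectiveness is not identified at any sample size, and an incremental estimate for Tromsø or Harstad is calculable but confounded with hospital. This follows from the stated design and needs no assumed figure. The p-value for the ICER has no useful null, and its 95% interval is bounded only for a QALY difference above about 0.014 to 0.023. That range rests on 600 per arm and an assumed QALY SD of 0.12 to 0.20. It ignores baseline adjustment, which would tend to lower it, and clustering by hospital, which would raise it. The true QALY difference is unknown; 0.01 is only an illustration.

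A reader might infer that the design can validly give none of the promised economic outputs. The article does not support that: site contrasts can be calculated, ICER intervals can be sound, and the societal issue is only an unstated source in a condensed article. The consequences are confined to secondary economic reporting and do not touch the primary outcome, but the changes should be made.

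**What to change.** 1. Define the hospital-specific increment as the patients of each PACT hospital against their own matched controls. Label it a between-hospital contrast and state that PACT and hospital effects are not separable in it. For Bodø and Narvik report mean costs and QALYs only. Drop the claim to model variability in cost effectiveness between centres.
2. Drop the p-value for the ICER. Make incremental net monetary benefit with a 95% CI across the willingness-to-pay range, together with the acceptability curve, the reported inference. Give the ICER as a point estimate, and add an interval only when the QALY difference is clearly non-zero, for example when its own 95% CI excludes zero.
3. Minor: name the source of the societal costs (collected items or stated assumptions), or delete that sensitivity analysis. The Status section says that no patients had been enrolled at the time of writing, so questionnaire items could still be added then.

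The cost is a few changed sentences and slightly more analysis and reporting work, within the NMB framework already adopted. Only collecting societal costs would add to data collection.
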